### Sample size calculation

The necessary number of study participants follows from the anticipated effects in the three co-primary outcomes. In Gossmann et al. [7], the observed mean eGFR was 92 mL/min/1.73m^2^ before and 71 mL/min/1.73m^2^ after donation (relative difference |Δrel| ≈ 23%), each with a standard deviation of 15–20 mL/min/1.73m^2^. Similar results were obtained in the study by Ibrahim et al. [9]. In Kroencke et al. [21], average SF-36 “physical health” summary scores were observed at successive measurement time points, that vary between 51 and 56 units (|Δrel| ≈ 10%), each with a standard deviation of up to 8 units. The SF-36 “mental health” summary score amounted to around 53 units and relatively stable in time, with standard deviations of 6.3, 8.9 and 7.7 units at the three consecutive measurement time points. Similar results were obtained in the retrospective study of Wiedebusch et al. [32], who reported SF-36 summary scores of 51–52 units with a standard deviation of 9 units 6 months after surgery. In case of all outcomes, measures obtained from an individual study participant at successive measurement time points are assumed to be positively correlated. A total number of 320 pairs of kidney donors and recipients will be included in the study, resulting in 2 × 320 = 640 study participants. A number of 200 pairs of kidney donors and recipients is expected to provide evaluable data. With this sample size, the above reported differences in the co-primary outcomes eGFR and SF-36 “physical health” summary score can be detected with a power of > 90% in the primary statistical analysis. For the third co-primary outcome SF-36 “mental health” summary score, possible mean differences between successive measurement time points in the order of 3 units (|Δrel| ≈ 6%) can be detected with a power of > 85%. Power calculations were performed using the SAS software.

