### Measurement time points

Living kidney donors and the associated organ recipients are examined at four time points (T0, T1, T2, T3) before donation and during the regular follow-up visits required by the transplant centers. All data for the baseline assessment (T0) is collected immediately (1–2 days) before the donation in order to avoid in the case of the earlier baseline assessment (e.g. during the preparation process for the donation) the possible donors’ concern that they might be considered as not suitable for donation because of their answers. The data collection for all time points corresponds with the clinical routine process and is imbedded into the usual care practice of LKD. The time points of measurement of the study are shown in Fig. 1.

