In the primary statistical analysis, the following hypothesis test problems are established in an analogous manner in case of each of the three co-primary outcomes eGFR, SF-36 “physical health” and “mental health” summary score. Denote μ_i_ (*i* = 1,2,3) the expected values of the respective outcome at three consecutive follow-up visits T1, T2, and T3. The global null hypothesis H_0_:μ_1_ = μ_2_ = μ_3_ is established and tested against the alternative H_1_:∃(i,j)∈{1,2,3}: μ_i_ ≠ μ_j_ in order to detect any kind of mean changes over time. Beyond the global null hypothesis, pairwise comparisons of expected values μ_i_ (i = 1,2,3) are performed by testing the null hypotheses H_0_^(12)^: μ_1_ = μ_2_, H_0_^(13)^: μ_1_ = μ_3_ und H_0_^(23)^: μ_2_ = μ_3_ against the corresponding two-sided alternatives. The overall multiple significance level across the three co-primary outcomes is set to α = 0.05. In order to keep this significance level, Bonferroni adjustment is applied. Each of the three co-primary outcomes is assigned the local significance level α_loc_ = 0.05/3 = 0.0167, i.e., α_loc_^eGFR^ = 0.0167, α_loc_^SF36phys^ = 0.0167 and α_loc_^SF36mental^ = 0.0167. Within each of the three co-primary outcomes, the following multiple testing strategy is applied, that is derived from the closed test principle. Denote the calculated *p*-values of the pairwise null hypotheses H_0_^(ij)^: μ_i_ = μ_j_ (i,j∈{1,2,3}) p_ij_ and the p-value of the global null hypothesis H_0_:μ_1_ = μ_2_ = μ_3_ p_123_. Any specific pairwise null hypothesis H_0_^(ij)^ is rejected if and only if both p_ij_ ≤ 0.0167 and p_123_ ≤ 0.0167. This multiple testing strategy provides strong control of the family-wise type I error rate α_loc_ = 0.0167. Each of the above null hypotheses will be tested using *Wald* type tests of the respective contrasts in the final established *Mixed Linear Model*. Point estimators of all contrasts will be supplemented by (two-sided) confidence intervals. The primary efficacy analysis provides confirmatory statistical evidence. Secondary outcomes will be analyzed using descriptive and inferential statistical methods. Appropriate tests will be applied for pre-specified hypotheses. Point estimates and associated 95% confidence intervals will be provided.

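### The >90% power stated for eGFR belongs to a before-versus-after-donation difference that the primary hypotheses do not test, so power for eGFR change between T1, T2 and T3 is unsupported

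*Protocol article*

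**What the plan says.** Under Sample size calculation, the only eGFR effect comes from a cited donor study: "the observed mean eGFR was 92 mL/min/1.73m^2^ before and 71 mL/min/1.73m^2^ after donation", with a standard deviation of 15–20 in each case. About 200 donor-recipient pairs are expected to be evaluable. The section concludes that the reported eGFR and SF-36 physical differences "can be detected with a power of > 90% in the primary statistical analysis".

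Under Statistical analysis, the primary hypotheses are built on "the expected values of the respective outcome at three consecutive follow-up visits T1, T2, and T3". The global null sets these three means equal, and the three pairwise nulls compare them two at a time "against the corresponding two-sided alternatives". A pairwise null "is rejected if and only if both p_ij_ ≤ 0.0167 and p_123_ ≤ 0.0167". The same section lists the baseline value of each outcome first among the independent variables of the mixed model.

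On timing, the Abstract (Methods/design) places the follow-up assessments 8 weeks, 6 months and 12 months after donation. Measurement time points states: "All data for the baseline assessment (T0) is collected immediately (1–2 days) before the donation".

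**The concern.** The power statement names the primary analysis as the place where the 21-unit eGFR fall will be detected. That analysis has no pre-donation mean, so no primary test can detect the fall. The two sections disagree about which contrast the trial was sized for.

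The eGFR of the donor is a confirmatory co-primary outcome. If T1, T2 and T3 do not differ significantly, a reader who trusts the power statement will take this as the result of a test with more than 90% power. No post-donation eGFR change was planned for, so that reading has no basis. The mismatch also means that the effect used for planning, the loss from before to after donation, is not tested in the confirmatory analysis as written.

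**Working it through.** **Inputs**

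- Overall level: "The overall multiple significance level across the three co-primary outcomes is set to α = 0.05". Local level: "Each of the three co-primary outcomes is assigned the local significance level α_loc_ = 0.05/3 = 0.0167" (Statistical analysis). Two-sided critical value: z = 2.394.
- Evaluable donors n = 200; eGFR SD 15–20; reported difference 92 − 71 = 21 (Sample size calculation).
- Within-donor correlation ρ: described only as positive. The values used below are assumptions.

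**Step 1: reproduce the stated figure.** The standard error of a paired difference is SD·√(2(1−ρ)/n). In the least favourable case (SD 20, ρ = 0) it is 20·√(2/200) = 2.0. Then 21/2.0 = 10.5, and power = Φ(10.5 − 2.394) = Φ(8.1), essentially 100%. A smaller SD or a positive correlation raises it further. So >90% is correct as a lower bound for a 21-unit contrast.

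**Step 2: look for that contrast in the primary analysis.** The hypotheses are μ1 = μ2 = μ3 and its three pairs, all after donation. T0 is not among them. Using baseline as a covariate does not bring it in: a baseline main effect is constant within a donor and cancels from any difference between T1, T2 and T3.

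**Step 3: what the stated test can detect.** The article gives no post-donation eGFR difference, so no single corrected power exists. The difference detectable pairwise with 90% power is

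(2.394 + 1.282)·SD·√(2(1−ρ)/200)

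| Assumed ρ | SD 15 | SD 20 |
|---|---|---|
| 0 | 5.51 | 7.35 |
| 0.5 | 3.90 | 5.20 |
| 0.8 | 2.47 | 3.29 |
| 0.9 | 1.74 | 2.32 |

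**Step 4: power over a range of assumed T1–T3 differences.** None of these differences comes from the document. The global column assumes that T2 lies halfway between T1 and T3. Because both tests must be significant, neither column alone is the power of the full rule; the joint power cannot exceed the smaller of the two. Each cell runs from SD 20 to SD 15.

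| T1–T3 difference | Pairwise, ρ 0.5 | Global, ρ 0.5 | Pairwise, ρ 0.8 | Global, ρ 0.8 |
|---|---|---|---|---|
| 1 | 5–7% | 4–5% | 10–18% | 7–13% |
| 2 | 16–30% | 11–22% | 43–71% | 33–60% |
| 3 | 39–66% | 29–55% | 83–98% | 73–96% |
| 4 | 66–91% | 55–85% | 98–100% | 96–100% |
| 5 | 87–99% | 79–97% | about 100% | about 100% |

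A course of 71, 72, 73, for example, is the 2-unit row, and it is an assumption like every other row.

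**Step 5: would the statement hold if T0 were tested?** Take means of 92, 71, 71, 71 (a plateau, assumed for illustration), SD 20 and ρ = 0. The noncentrality of the four-mean global test is 200 × (21² × 3/4)/20² = 200 × 330.75/400 ≈ 165, so power is essentially 100%. The >90% claim would then hold.

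**The case against.** The best reply is that nothing has been miscalculated. The >90% is true for 21 units, and without a stated post-donation effect nobody can show that the T1–T3 test has less than 90% power. The detectable differences of roughly 2.5 to 7.4 mL/min/1.73m² (correlation 0.8 down to 0) are far from those of a powerless test. If T0 was meant to be compared, the fault lies in the hypotheses and the power statement is right. All of this stands, and it limits the point to a mismatch between two sections. It does not remove the mismatch, because both statements are explicit and one of them must change.

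A reader might infer three stronger things that the document does not support.

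- *That the test has almost no power.* This depends wholly on the post-donation change one assumes, as Step 4 shows.
- *That power would be only 1.67% if eGFR stays level after donation.* That figure is the type I error under a true null. Failing to reject would then be the correct result.
- *That the SF-36 physical score has the same fault.* Its 51–56 range is described as varying over consecutive assessments, and the article does not say whether one of them precedes donation. Background groups the source with studies that found early reductions, and adds that most such reductions had disappeared later. That fits a difference between post-donation visits just as well. The document cannot settle it.

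**Conclusion.** The point holds for eGFR only. The stated >90% power refers to a contrast outside the primary hypotheses. It is inapplicable to the test as written, and power for eGFR change among T1, T2 and T3 is unsupported. It is not shown to be false or to be below 90%.

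The gap is between a 21-unit difference, detected almost with certainty, and a post-donation difference of unstated size, for which the 90% threshold lies at about 4 to 5 units if the correlation is 0.5. That threshold rests on 200 evaluable donors, equal SDs of 15–20, an assumed correlation and the pairwise test alone. The finding of a mismatch rests on none of these assumptions, only on the two sections read together. It should be corrected, because a null eGFR result would be interpreted against this figure.

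**What to change.** Choose one, for eGFR only.

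(a) Keep the T1–T3 hypotheses. Replace the >90% statement for eGFR with the post-donation difference detectable with 90% power at n = 200 and two-sided 0.0167, and state the assumed SD and within-donor correlation. On the figures above this is about 5.5–7.4 at correlation 0, 3.9–5.2 at 0.5 and 2.5–3.3 at 0.8. Say that these are pairwise figures and that the global test must be significant too. Cost: one recalculated paragraph.

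(b) Add T0-versus-follow-up contrasts to the primary eGFR hypotheses. T0 must then be modelled as an outcome visit rather than as a covariate. The closed test must also be rebuilt for four means, because the rule of one global test plus pairwise tests is complete only for three. With four means the intermediate intersections (three means equal, or two separate pairs equal) also have to be tested. The >90% statement for 21 units then holds. Cost: an amendment to the hypotheses, model and multiplicity rule. Since Participants reports that 320 donors have already been included, the change should be dated and made before outcome data are analysed.

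Neither option changes enrolment.

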## Discussion

The aim of the SoLKiD study is to investigate the physical and psychosocial outcomes of living kidney donors during a 12-months course after donor nephrectomy in a prospective multicenter design. It aims to answer the question, which health risks might arise from the elective removal of one kidney from a healthy donor. The interdisciplinary approach enables the assessment of a broad number of physical and psychosocial health status outcomes in order to provide a comprehensive overview of the consequences and the natural course after LKD. Studies on the physical consequences of LKD show divergent results. They reported, on the one hand, an age-dependent decrease of the eGFR of up to 30% within 10 years after donation especially in female donors [7–10]. On the other hand, they did not find a higher rate of renal insufficiency, compared to the general population [9]. However, these studies were mostly based on young and healthy donors. Register studies in the US and Norway showed reduced life expectancy and higher rates of ESRD than in the healthy population basically able to donate [11, 12]. Regarding arterial hypertension as the most important risk factor in the general population for cardiovascular morbidity and mortality, about 15% of donors develop it after kidney donation (in Germany up to 10%) [14, 33]. Data from the Norwegian health registers showed a prevalence of hypertension 5 years after donation of about 27% [15]. In contrast, another study did not find an increased prevalence of hypertension in donors compared to their non-nephrectomized twins [16]. Such differing results could be explained by varying observation times, in the study by Mjoen et al. 5 years after LKD, in the study by Najarian et al. 20 years after LKD [15, 16]. Some studies found an increased cardiovascular mortality especially in the subgroup of older donors with declining eGFR [34, 35]. Generally speaking, findings about the increased mortality in living kidney donors reported above cannot be maintained because of their methodological limitations, such as age difference between donors and controls, lack of matching of age [36], or selected donor population (donors and recipients with immune-mediated kidney disease are biologically related or African Americans) [13]. Furthermore, a matched cohort study of Reese et al. with a sample of 5152 donors aged > 55 years old showed that there are no differences regarding mortality between older kidney donors and healthy participants [37]. Whether a donor with pre-existing and treated hypertension can be accepted for donation must be considered carefully. One single center study with a low number of older and obese donors demonstrated worse renal function compared to non-obese donors [38]. Especially older donors seem to have an increased obesity-associated risk for hypertension, which cannot be attributed to nephrectomy alone [39, 40]. There are also no data regarding gender-specific consequences of donation. In the US, a trend already indicates that donors are increasingly older, medically complex ill, overweight, and often hypertensive or even have pre-diabetes [39, 41]. Thus, more donors with so-called “isolated medical abnormalities” are accepted.

Studies on the QoL of donors after LKD found similar or slightly higher scores compared to the general population [18, 19, 42]. High QoL is associated with a positive attitude towards the provided donation [9, 29, 32, 42–44], but little is known about risk factors for adverse psychosocial outcomes. Because previous studies were mostly conducted retrospectively, a large variation in the follow-up time after donation (up to 48 years) exists, introducing a potential for recall bias. Many studies were cross-sectional in design allowing no conclusion on the change in QoL after donation. Thus, because of methodological limitations in several prior studies, their results cannot be generalized. The SoLKiD study with its prospective, multicenter design will add to the outcome data of living kidney donors. In view of an ongoing controversial debate about transplantation medicine in Germany, which is likely to further reduce the post mortem organ availability, and also because of the debate on the allowable scope of living donation, the SoLKiD results can provide a valuable database for transplant professionals to facilitate the discussion about potential risks, as well as for patients and their families to help them reach an informed decision about the donation.
